### Environmental sustainability methodology and analysis

The environmental impact of the service will be assessed using CO_2_eq and estimates of direct waste, including that arising from patient travel. Using the SusQI framework, CO_2_eq will be mapped across the different clinic iterations, with standard regression analysis used to compare the carbon output of RAPID ENT setups with that of traditional clinics. CO_2_eq will include patient travel, clinic energy use (capture booth/otoscope/endoscope, computing) and consumables. Distance will be calculated by patients’ estimates and postcode. Emission factors will be drawn from current UK Government conversion factors; uncertainty will be propagated via non-parametric bootstrap.

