The remote service uses trained nursing or physician associate staff to ‘collect’ the necessary patient data, for example, supervision of tablet history collection and boothless audiogram, and perform video of patient ears/nose, thereby allowing consultants to review this information and diagnose and manage patients remotely (figure 1). Audiometric testing will be performed using calibrated boothless audiometers developed by hearX Group (Pretoria, Gauteng, South Africa). These devices are commercially available systems that meet the required regulatory and calibration international standards for clinical use (ISO 8253-1/ISO 389 Series/IEC 60 645-1/ANSI S3.6) and are CE-marked registered and certified in Europe. The company’s regulatory standards are available in detail on their webpage: https://www.hearxgroup.com/products/heartest. This enables optimisation of resources through face-to-face, technician-delivered clinics in varied locations with consultants providing opinions flexibly. The service can be placed in different locations, closer to the patients, reducing travel and environmental impact. The University Hospitals Birmingham (UHB) NHS Foundation Trust has approved the introduction of this novel pathway into their outpatient referral pathway from primary to secondary care, currently facilitating the delivery of Otology and Rhinology clinics.

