### Recruitment

Patients referred from primary care to ENT specialist services and attending either a conventional face-to-face consultant-led clinic or a remote clinic will be recruited into the study. We will send an invitation letter explaining the purpose of the study to the patients, along with their clinic invitation letter, and potential participants will be approached prior to their initial clinic appointment.

On their attendance at clinic, patients will be approached by a member of the healthcare team and will be given the study information package and offered the opportunity to ask questions and discuss their potential participation in the study. For those patients who agree to take part, this will be documented in their medical records and the research team will begin informed consent procedures.

Patients will not be randomised, and the study will not have any influence on the allocation of patients to the traditional or the remote pathway, which will be arranged by UHB, on a weekly basis, according to clinical priority and waiting length per referral. The clinic allocation process is regulated by the hospital and patients are allocated in consecutive order to either a face-to-face or a remote clinic, until all the slots of that week have been filled, before booking patients for a different week. Patient prioritisation is made in the form of urgency, without reference to the method of clinic delivery. Patient demographics, disease severity or other characteristics are not used in regards to allocation to an in-person or remote clinic appointment.

This will ensure that selection bias will not be introduced on the patients seen in the remote pathway, compared with the cohort seen face-to-face. We will assess propensity scores for the patients and assess their propensity score weighting using logistic regression.

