This is an observational study, and we are not measuring the effect of an intervention. Our initial sample size calculations have been driven by similar pieces of implementation studies in the literature, looking into studies assessing non-inferiority interventions for remote/telehealth clinics, as well as assessing the potential financial benefit to the patients/service and the environmental impact,^11^,^15^ further informed by similar studies mapped through our team’s scoping review.^6^ Continuous sampling will be undertaken on both pathways until we reach a number of 150 participants from each group that have completed the initial questionnaires. The patients of the remote pathway will also be sent a follow-up questionnaire after their discharge, asking for their overall experience of the new service. The total of recruited participants will be expected to exceed the minimum of 300 we need for our analysis, and we will be allowing for a 10% attrition, as the current number for patients seen in face-to-face and remote clinics exceeds the 80 patients per cohort, per week. All the primary outcomes data will be extracted directly from the clinical notes of the patients, while the data of the secondary outcomes will be procured via questionnaires.

For the interviews, we will use a topic guide developed based on the existing literature and the research team’s experience of technology and innovation implementation, as well as service redesign.^16^,^18^ Through the interview process, we will investigate the experience of the different stakeholders involved in the remote pathway. We will undertake purposive sampling to select participants, expecting 30–35 participants in total, to allow for thematic saturation to take place.^19 20^ Participants in the interviews will be classified into two categories: patient participants and NHS staff. Recruitment will continue until overall thematic saturation has been achieved within each group. Patients enrolled will be approached, after completing the remote clinic pathway, while clinicians, managers and the other stakeholders will be given participation leaflets and invited via email or in person to participate in the study through interviews. If non-English speakers participate in the interviews, interpreters will also be facilitating the process.

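### The travel part of the carbon comparison leaves each patient's distance to the alternative site unused, which costs precision, and the distance-to-clinic covariate could adjust the travel effect away

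*Protocol article*

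**What the plan says.** Environmental sustainability methodology and analysis defines the outcome: "CO_2_eq will include patient travel, clinic energy use (capture booth/otoscope/endoscope, computing) and consumables". The comparison is "standard regression analysis used to compare the carbon output of RAPID ENT setups with that of traditional clinics". On the travel input it says "Distance will be calculated by patients’ estimates and postcode", and on error "uncertainty will be propagated via non-parametric bootstrap".

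The Introduction names location as the source of the travel gain: "The service can be placed in different locations, closer to the patients, reducing travel and environmental impact". Project setting lists hospital outpatients, diagnostic hubs and primary care clinics, and Secondary outcomes asks for the footprint of both clinic models by location.

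Under Recruitment, sampling continues "until we reach a number of 150 participants from each group that have completed the initial questionnaires". The groups are separate sets of people: "Patients will not be randomised, and the study will not have any influence on the allocation of patients". The same section says that slots are filled consecutively and that patient characteristics do not decide who gets which kind of clinic.

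Quantitative analysis, which counts environmental sustainability among its outcomes, lists distance to clinic as an adjustment covariate. It does not say which clinic is meant.

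**The concern.** The travel effect of moving a clinic is a contrast between two places for one patient. A comparison of remote patients' journeys with other patients' journeys also carries the difference in where the two groups happen to live. A postcode locates each patient, so the distance to a site not attended is a look-up, and the stated method does not use it. The bootstrap describes the resulting noise but does not reduce it.

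The one stated adjustment that might help is ambiguous. Distance to the clinic attended is the very quantity through which clinic placement changes travel carbon, so adjusting for it removes the effect being estimated.

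At stake is the precision, and under one reading of the covariate the meaning, of the travel component. This matters most for the by-location results, where the 150 remote patients are divided among settings.

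**Working it through.** **Inputs from the article.** 150 per group, 2 × 150 = 300; different patients in each group; postcode collected; several kinds of site. There is no distance, SD, effect or power for carbon, so the article has no precision figure to reproduce.

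**Assumed.** 300 patients spread evenly over a disc of radius 12 km, hospital at the centre, remote sites elsewhere, each patient using the nearest remote site unless stated.

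**Formula.** Let s_H and s_R be the SDs of a patient's distance to hospital and remote site, and ρ their correlation.

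- Between groups: V = (s_H² + s_R²)/150
- Within patient, all 300 postcodes: V = (s_H² + s_R² − 2ρ s_H s_R)/300

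With equal SDs the variance ratio is (1 − ρ)/2, and the SE ratio is its square root:

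| ρ | −0.5 | 0 | 0.3 | 0.5 | 0.7 | 0.9 |
|---|---|---|---|---|---|---|
| SE ratio | 0.87 | 0.71 | 0.59 | 0.50 | 0.39 | 0.22 |

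With SD ratios of 0.3 to 0.8 and ρ of 0 to 0.6, the SE ratio runs from 0.46 to 0.71. If only the 150 remote patients were used, the variance ratio would be 1 − ρ, a gain only when ρ > 0.

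**Worked case, one remote site at 6 km.**

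- Hospital: mean 2 × 12/3 = 8 km; mean square 12²/2 = 72; variance 72 − 64 = 8; SD 2.83.
- Remote site: mean square 72 + 6² = 108; mean 8 + 2.96/2 = 9.48 (2.96 km is the simulated round-trip difference); variance 108 − 89.87 = 18.13; SD 4.26.
- Simulated ρ = 0.47.
- Between groups: √[(8 + 18.13)/150] = 0.42 km.
- Within patient: √[(26.13 − 2 × 0.47 × 2.83 × 4.26)/300] = √(14.80/300) = 0.22 km.

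**Simulation, SE of the one-way difference (km); runs differ by about 0.01.**

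| Layout | Between groups | Adjusted for home-to-hospital distance | Within patient |
|---|---|---|---|
| One site at 6 km | 0.41 | 0.31 | 0.22 |
| Three sites at 7 km | 0.29 | 0.20 | 0.16 |
| Hospital and site on opposite sides (ρ about −0.35) | 0.45–0.48 | not run | 0.37–0.40 |
| Remote clinic at the hospital | 0.32 | 0.00 | 0.00 |

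Adjusting for both home-to-hospital and home-to-remote distance recovers nearly all the gain: round-trip SD 0.45, against 0.44 within patient (one site).

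**Varying visits.** If 40% of traditional and 30% of remote patients make a second visit (assumed), the SD of total round-trip km goes from 1.51 to 1.14 with one site (ratio 0.75) and from 1.10 to 0.86 with three (ratio 0.78).

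**Adjusting for the clinic attended.** For one visit, round-trip km is exactly twice that distance, so the group coefficient must be zero. It was 0.00 in every layout, against true differences of +2.96 km (one site) and −6.16 km (three sites). With varying visits it was −1.70 against +2.25, and −1.20 against −9.62.

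**If booking depended on location.** Suppose the log-odds of a remote slot fall by 0.1 for each extra km of remote over hospital distance (assumed, one site). The unadjusted estimate was 1.95 km against a truth of 2.95, the estimate adjusted for both distances 3.10, and the within-patient estimate 2.95. With allocation unrelated to residence, the unadjusted estimate was 2.94 against 2.96.

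**Choice of alternative site.** With four sites at 6 km, a nearest-site rule gives −3.7 km one way. If patients take any open slot regardless of residence, the true difference is +1.5 km. The wrong rule reverses the sign and errs by 3.7 + 1.5 = 5.2 km.

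**The case against.** The strongest reply is that comparing observed journeys answers the question the article asks, namely the footprint of each pathway as delivered. A within-patient contrast replaces part of that with a modelled journey to a site never attended. It needs a rule for the alternative site, assumes the same travel mode, and still leaves visits per pathway to a between-group comparison. Site modelling is also detail that an article may leave to a fuller plan.

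Much of this stands. Observed journeys should remain the outcome, and the four-site example shows that a careless rule can do more harm than the noise it removes. What does not stand is that the plan already deals with residence. It states a between-patient method, the bootstrap does not shrink the error, and the listed covariate is unhelpful or harmful unless it means distance to a common reference site.

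Three stronger readings are tempting and not supported:

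- A reader might infer that geography biases the carbon result. Recruitment says characteristics do not decide the clinic type, and no passage describes catchment-based booking or patients choosing a local slot. Chance imbalance is already inside the between-group standard error and should not be counted again as a shift.
- A reader might infer that each postcode has its own remote site, so that the within-patient difference could simply replace the regression. No passage assigns postcodes to sites.
- A reader might infer that patients' guesses are blended with postcode distance. The sentence does not say how the two are combined.

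**Conclusion.** The point holds as a loss of precision in the travel component, together with a covariate whose meaning must be fixed. The within-patient SE is roughly 0.4 to 0.9 of the between-group SE for ρ between 0.7 and −0.5. It is lower still when the remote site is at or very near the hospital, and about 0.75 to 0.78 in the two layouts above once visit numbers vary. All of these figures rest on assumed geography, because the article gives no distances, SDs or site locations. Bias follows only if booking or consent depends on where patients live, which the article does not indicate. If distance to clinic means the clinic attended, the adjusted model would not estimate the travel effect at all. Clinic energy and consumables are unaffected, and carbon is a secondary outcome, so the change is worthwhile but not critical.

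**What to change.** 1. For every participant in both groups, compute postcode distance to the hospital clinic and to the remote site or sites in use.
2. Keep observed journeys as the travel CO2eq outcome. In that model, replace distance to the clinic attended with these home-to-site distances, and say so wherever the covariate list is given.
3. Report the within-patient per-visit difference alongside. For remote patients use the site actually attended. For traditional patients prespecify a rule that follows how slots are really booked: average over the sites in use if booking ignores residence, rather than assuming the nearest site.
4. Bootstrap by patient, and combine the per-visit difference with visits per pathway.
5. Say how patients' own distance estimates are used alongside postcode distance.

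Cost: one or a few extra distance look-ups per patient and no new data collection. The within-patient figure needs the stated site rule and assumes unchanged travel mode; vary both in sensitivity analysis.

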### Patient and public involvement

Patient and public involvement and engagement (PPIE) group has been a crucial component of this study, and a previous dedicated group contributed to the initial design of the current project plan and project aspirations, in line with the GRIPP2 guidance.^25^ The study-specific group that has been employed since the initial iterations of this study consisted of members of the UHB rhinology and audiology PPIE groups, while external contribution from the “1000 Elders” UoB PPIE group, using focus groups. They have been involved in reviewing our proposal, helping us identify the patients’ priorities and what accounts to a “successful” clinical encounter to them, as well as contributing to the final version of this protocol. Following the principles of co-design and co-production, the PPIE lead contributed to previously published work on the application of PPIE groups in ear and hearing research, a field with no previous published literature.^26^

## Ethics and dissemination

UoB is the sponsor of this study (study number RG_25-016) and this study received ethical approval by the Health Research Authority on the 2nd of October 2025 (IRAS 350908, REC reference 25/SW/0116), contact email: [contact]. This study has been publicly registered in the Open Science Framework database: https://doi.org/10.17605/OSF.IO/BRQC3.

Results will be disseminated more widely by presentation at national and international conferences, such as the Confederation of European Otorhinolaryngology, Head and Neck Surgery Conference, and publication in open access, peer-reviewed journals. We will also communicate our findings through the social media sites of UoB and UHB.

### Data availability

Data are available upon reasonable request. De-identified participant data will be stored in UHB and UoB cloud. Requests for access can be made through the corresponding author and upon review by the sponsor of the study, access and reuse will be considered.
